### Information leaflet

Three different information leaflets will be used, one for each arm. The information leaflet is an updated version of the leaflet used in previous CRC screening trials in the Amsterdam and Rijnmond region and modified for the screening methods studied. The leaflet is based on the principles of informed-choice, aiming to enable all invited persons to make a well-informed decision whether or not to participate. The leaflet consists of information on CRC in general, the advantages and possible risks of the screening method and on the follow-up in case of a positive test result.

### Prior consultation

Persons allocated to colonoscopy screening are invited for a prior consultation either by telephone or at the outpatient clinic. Prior to CT colonography, all invited individuals will receive a consultation by telephone. During the consultation, they are informed about the screening procedure, bowel preparation, possible risks and the follow-up in case of a positive test result. A standardized questionnaire is used to check on contra-indications and/or exclusion criteria. If additional information is needed regarding a possible exclusion criterion or contra-indication for the screening procedure, the general practitioner or medical specialist will be contacted for further information or the individual selected for intake by telephone will be invited for a visit at the outpatient clinic. Individuals without contraindications will be scheduled for screening at the regional CRC-screening centre. Subsequently, all colonoscopy screening participants will be asked to perform an immunochemical FOBT.

### Informed consent

Informed consent will be discussed during the prior consultation. All participants are instructed to return the informed consent form by mail before the scheduled screening procedure.

### Colonoscopy

All colonoscopies will be performed at one of the two participating centres by gastroenterologists with an experience of 500 or more colonoscopies. The colonoscopy will be performed taking the standard quality aspects into account defined by the American Society for Gastrointestinal Endoscopy[38]. All participants are prepared by a low fibre diet and by oral intake of 2 L of transparent fluid and 2 L of hypertonic polyethylene glycol solution (Moviprep; Norgine bv, Amsterdam, The Netherlands) at home. The procedures are performed under conscious sedation using intravenous midazolam (Dormicum, Actavis, Baarn, The Netherlands) and fentanyl (Bipharma, Weesp, The Netherlands) at the discretion of the participant and the endoscopist. In case of poor bowel preparation the colonoscopy is interrupted and postponed. Cecal intubation by the colonoscope is confirmed by still images of the appendiceal orifice and ileocecal valve or by intubation of the ileum. Insertion and withdrawal times will be separately recorded. At the start of withdrawal of the endoscope, butylscopalamine bromide (Buscopan, Boehringer Ingelheim bv, Alkmaar, The Netherlands) will be given intravenously at the discretion of the endoscopist to reduce colonic motility and repeated if necessary. Inspection on withdrawal of the endoscope will be at least 6 minutes[39]. All detected lesions will be removed during the same procedure if possible. If immediate endoscopic treatment is impossible, biopsies will be obtained and pathological assessment of these tissue samples will provide a definitive diagnosis.

#### Lesions

Of all detected lesions during colonoscopy the size (millimetres), morphology (sessile, pedunculated, flat or depressed), localization (distance from the anus, segment of the colon) and macroscopic aspect (hyperplastic, adenomatous, carcinomatous) will be noted. The size of each lesion is measured using an open biopsy forceps with 7 mm span. Furthermore, data on diagnostic or therapeutic procedure (biopsy, piecemeal polypectomy, coagulation or cold-snare total polypectomy), macroscopic involvement of margins, use of saline and/or epinephrine, and time needed for polypectomy will be recorded.

#### Pathology

Histology will be defined according to the Vienna criteria[40]. Dysplasia will be defined as either low grade or high grade and all lesions will be classified into hyperplastic, serrated, tubular, tubulovillous, villous or carcinoma lesion. Histopathology will be processed and stained using standard methods and will be evaluated by two expert pathologists (one in each centre). All advanced neoplasias and a random selection of 10% of all other lesions evaluated in each centre will be revised by the pathologist of the other centre. In case of inconsistency, the slides will be reviewed together to come to a definitive diagnosis.

### CT colonography

The preparation for CT colonography includes two times 50 mL of iodinated contrast agent (Telebrix, Guerbet, Aulnay sous Bois, France) for tagging on the day prior to the study and 50 mL 1.5 hour before the examination, combined with a low-residue diet. This regimen resulted in high image quality not distinct from a full bowel preparation[41]. Bowel preparation with tagging is now indicated as best practice in the recently published international CT colonography standards[42]. Colonic distension will be obtained with an automatic carbon dioxide insufflator (PROTOCO2L, Bracco, EZEM, Lake Success, USA) after intravenous administration of 1 ml butylscopalamine bromide. If butylscopalamine is contraindicated, 1 mg of glucagonhydrochloride (GlucaGen, Novo Nordisk A'S, Bagsvaerd, Denmark) will be used intravenously. If both butylscopalamine bromide and glucagonhydrochloride are contraindicated, CT colonography examination will be performed without bowel relaxants. CT colonography will be performed with a 64-slice CT scanner in one of the two participating centres by qualified and experienced personnel. Images will be obtained in both the supine and prone position, using a low dose protocol with the following specifications: collimation 64 × 0.625 mm, slice thickness 0.9 mm, reconstruction interval 0.7 mm, tube voltage 120 kV and 25 ref mAs supine and prone.

Each CT colonography is evaluated by one of the three experienced physicians (two abdominal radiologists, one research fellow) as well as two of the four experienced technicians (prior experience ≥200 CT colonography examinations with colonoscopic verification). Image processing and interpretation is performed with the use of a non-commercially available CT colonography workstation (View Forum, Demo version R6.1V1L1, Philips, Eindhoven, The Netherlands). Primary 2D read will be used, with endoluminal 3D problem solving and the use of computer assisted detection (CAD) as a secondary read. Lesion size will be measured on 3D images, unless there is too much faecal material around the polyp, in that case 2D measurements will be used.

#### Lesions

Both intra- and extracolonic findings will be recorded. A true positive intracolonic CT colonography finding is defined as a CT colonography lesion of at least 6 mm that is found in the same or adjacent segment on the colonoscopy with the size of the lesion at least <50% margin of error.

Diminutive polyps (5 mm and smaller) will be ignored as the chance for malignancy is very low. Of all intracolonic lesions ≥ 6 mm, data on certainty (25%, 50%, 75% and 100%), size, location and morphology (sessile, pedunculated, flat) will be documented. If referred for colonoscopy, CT colonography results will be verified using segmental unblinding and histopathology.

Extracolonic structures will be examined using the C-RADS classification[43]. An extracolonic lesion of C-RADS E3 (likely unimportant finding, incompletely characterized) or E4 (potentially important finding) is considered to be clinically relevant.

### Complications

Complications will be registered until 30 days after the screening procedure. Complications of CT colonography are defined as all complications occurring during CT colonography as well as all complications of colonoscopy in CT colonography positives. Of all complications the timing, severity, relation to the procedure, treatment and outcome will be reported. All participants will be interviewed by telephone to ensure accurate complication registry.

### Follow-up after positive test result

#### Colonoscopy

All participants will be informed about the result of colonoscopy on the day of the procedure. In the case of polyps or cancer, histopathological assessment of tissue samples will provide a definitive diagnosis and participants will be informed about the results within 2 weeks. Advice regarding surveillance colonoscopy will be given to persons according to the Dutch Institute for Healthcare Improvement (CBO) consensus[44]. In case of cancer, the patient is invited at the outpatient clinic and referred to a gastroenterologist or surgeon for further treatment. The general practitioner and participant will receive a letter about the results of the colonoscopy and corresponding follow-up if needed after two weeks.

#### CT colonography

All participants will be informed by telephone about the results of CT colonography within 2 weeks. Both the participant and the general practitioner will receive a letter by mail with the findings at CT colonography. Individuals with one or more lesions ≥10 mm at CT colonography will be referred for colonoscopy, while individuals with only lesions 6-9 mm in size will be advised to undergo surveillance CT colonography. Surveillance CT colonography will be advised after 1.5 years when there are three or more 6-9 mm lesions and 3 years when there are one or two 6-9 mm lesions. If referral for colonoscopy is needed, the participant will be invited for a visit at the outpatient clinic where information is given on the consequences of the positive test result and if there are no contraindications a colonoscopy will be advised. If the participant consents, a colonoscopy will be performed within the following two weeks. Patients with relevant extracolonic findings will be invited at the outpatient clinic and referred for corresponding follow-up[43].

### Questionnaires

At different time-points, questionnaires will be provided. The first questionnaire is sent after the prior consultation to all subjects scheduled for the screening test to assess the following items: demographic and socioeconomic status, satisfaction of the prior consultation, reasons for participation, level of informed choice and expected burden of the screening procedure (items 1-5, see below). The same questionnaire is sent to all subjects not responding to the first invitation (non-respondents), together with the reminder, and to all non-participants to obtain information about the reasons of non-participation. In case of low response, 10% of non-respondents will be contacted by telephone to assess a shortened version of this questionnaire. A second questionnaire is sent to participants two weeks after the screening test and will contain questions about the perceived burden of the screening method (item 5).

#### 1) Demographic and socioeconomic status

Baseline characteristics as age, gender, marital status, ethnicity, education and employment will be collected.

#### 2) Satisfaction of the prior consultation

To evaluate the satisfaction of the prior consultation by telephone compared with the prior consultation at the outpatient clinic, items are included based on an existing patient-satisfaction questionnaire[45].

#### 3) Reasons for (non-)participation and understanding of the information leaflet

In the first and second Dutch pilots on screening for colorectal cancer with FOBT,[36,46,47] a questionnaire has been developed to collect data on awareness of CRC, reasons for (non-) participation and clarity and readability of the information leaflet. As in the second round of FOBT screening, the Health Belief Model (HBM) is used as theoretical background to understand the reasons for (non-) participation[36,48]. The corresponding items are adjusted for this study.

#### 4) Informed choice

To evaluate the proportions of participants and non-participants who made their decision on the basis of an informed choice, it is required to assess the knowledge, attitude and uptake of the invited persons. Items concerning knowledge and attitude are derived from both Dutch FOBT pilots [13,36], and from the evaluation of prenatal and lung cancer screening in the Netherlands which is based on Marteau's measure of informed choice [49-51].

#### 5) Expected and perceived burden of the screening procedure

The experience of participants with the screening procedure is evaluated with a questionnaire assessing anxiety, embarrassment, pain and discomfort. The items assess the perception of participants regarding the bowel preparation and the burden of the screening procedure itself. Responses are scored on a standard formatted five-point Likert scale. Satisfaction with the screening procedure will be measured by items scored on a 4-point scale.

This questionnaire is based on questionnaires used in the first and second Dutch pilot for screening with FOBT[34,36] and on studies investigating the acceptance of CT colonography[34] and patient perception of diagnostic tests for faecal incontinence[52], as well as on previous discrete choice experiments showing that especially type of bowel preparation, risk education of CRC related death and length of screening interval influence CRC screening preferences[37].

### Cost-effectiveness

Cost-effectiveness will be evaluated by incorporating the final results in the validated MISCAN-colon screening model for cost-effectiveness. That model compares different methods of CRC screening in our country and is used to estimate the costs, colonoscopy and CT colonography capacity requirements and effects of colonoscopy and CT colonography screening versus other screening programmes[53].

### Ethical approval

Ethical approval was obtained from the Dutch Health Council (2009/03WBO, The Hague, The Netherlands).

### Data analysis

We will calculate the participation rate as the number of participants undergoing the screening test relative to the total number of all eligible invitees. We will compare the participation rate between the three screening programmes, and express it as relative participation rates, calculating corresponding 95% confidence intervals, using colonoscopy screening with a prior consultation at the outpatient clinic as the reference strategy.

We will test the null hypothesis of no difference in participation rate using chi-square test statistics. We will also calculate a conditional relative participation rate using logistic regression modelling, accounting for baseline variables. If the overall hypothesis of no difference is rejected, we will test the null hypothesis of a difference in mode of invitation to direct colonoscopy. Additionally, we will test the null hypothesis of no difference in participation between CT colonography screening and direct colonoscopy screening.

The detection rate of the screening test is defined as the proportion of screenees with detected advanced neoplasia. Advanced neoplasia comprises all carcinomas and advanced adenomas together. An advanced adenoma is defined as an adenoma ≥ 10 mm, with villous histology (≥25% villous) or with high grade dysplasia. The most advanced detected lesion per screenee will be used to calculate the detection rate.

The diagnostic yield per 100 invitees is defined as the proportion of screenees with detected advanced neoplasia relative to all eligible invitees.

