### Study design

This study will be a two-centre randomized controlled trial. A cohort of 7,500 persons of the Amsterdam and Rijnmond region will be randomly selected from the electronic database of the regional municipal administration registrations (Gemeentelijke Basis Administratie (GBA)). In total, 2,500 persons will be randomly selected to receive an invitation for colonoscopy screening with a prior consultation by telephone. Another 2,500 persons will be randomly selected to receive an invitation for colonoscopy screening with a prior consultation at the outpatient clinic. A third group of 2,500 persons will be randomly selected to receive an invitation for CT colonography, with a prior consultation by telephone [figure 1]. Randomization will be performed per household, stratified for age, sex and socio-economic status (SES).

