### Study population

Our study population consists of 7,500 individuals between 50 and 75 years of age living in our target areas. The selected areas comprise all SES-categories (very low, low, average, high and very high) and are based on data of Statistics Netherlands[3]. The target areas will not have been selected for previous pilot trials on CRC screening. Individuals with CRC symptoms in the previous three months (rectal blood loss and/or changed bowel habits) are advised in our information leaflet to consult their general practitioner and to not participate in screening. Persons who underwent full colonic examination in the previous 5 years (complete colonoscopy and/or double contrast barium enema) are also instructed not to participate and are excluded from the screening programme, as well as individuals planned for surveillance colonoscopy, because of personal history of colorectal cancer, colonic adenomas or inflammatory bowel disease (IBD)). Persons with a severe or terminal disease with a life-expectancy of less than 5 years are excluded. Although pregnancy is not likely in this cohort, pregnant women are also excluded. For CT colonography, individuals exposed to ionizing radiation for research purposes within the previous 12 months and individuals with hyperthyroidism are excluded.

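### Participation and yield are divided by eligible invitees, a group settled after allocation and possibly differently by arm, so randomisation does not protect the comparison

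*Protocol article*

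**What the plan says.** The Data analysis section defines the primary outcome: "We will calculate the participation rate as the number of participants undergoing the screening test relative to the total number of all eligible invitees". It builds the yield on the same base: "The diagnostic yield per 100 invitees is defined as the proportion of screenees with detected advanced neoplasia relative to all eligible invitees".

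Four other statements in the protocol article determine how that denominator behaves:

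- **Allocation comes first.** Under Study design, "A cohort of 7,500 persons of the Amsterdam and Rijnmond region will be randomly selected from the electronic database", with 2,500 people assigned to each of three invitations.
- **Eligibility is checked later.** Under Prior consultation, "A standardized questionnaire is used to check on contra-indications and/or exclusion criteria". The exclusions listed under Study population are matters of medical history and condition.
- **The setting of that check is randomised.** "Persons allocated to colonoscopy screening are invited for a prior consultation either by telephone or at the outpatient clinic". CT colonography invitees are all consulted by telephone. A telephone invitee whose eligibility is unclear may be asked to come to the clinic.
- **Some criteria apply to one arm.** "For CT colonography, individuals exposed to ionizing radiation for research purposes within the previous 12 months and individuals with hyperthyroidism are excluded".

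The article names no analysis that uses everyone randomised and invited as the denominator.

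**The concern.** Randomisation makes the three groups of 2,500 comparable. It does not make comparable the subsets that remain after people are removed using information gathered later. Nothing in the article suggests that a municipal register holds colonoscopy history, surveillance plans or life expectancy. Such facts would emerge when an invitee replies or is consulted. An ineligible person who makes contact can be removed, while an ineligible person who stays silent may remain. Making contact is a step towards participation, so the denominator can move with the outcome. The consultation mode, the leaflet and part of the exclusion list also differ by arm.

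If the shares removed differ, the relative participation rate departs from 1 even when the same number per 2,500 attends in each arm. The primary comparison and the yield per 100 invitees are both affected. The yield is labelled by invitees but divided by eligible invitees.

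**Working it through.** **Inputs from the article.** 2,500 per arm (Study design); anticipated participation of 22.5% (colonoscopy, clinic consultation), 27.5% (colonoscopy, telephone) and 35% (CT colonography), and a significance level of 0.05 (Sample size).

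**Assumed inputs.** Every share ineligible, found or removed is an assumption, because the article gives none. Tests are two-sided at 0.05, use the normal approximation and treat invitees as independent. Household randomisation is ignored, so rejection rates are approximate.

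**1. The plan's own power figure.** For 22.5% versus 27.5%, the null SE is √(2 × 0.25 × 0.75 / 2,500) = 0.01225 and the alternative SE is √[(0.225 × 0.775 + 0.275 × 0.725) / 2,500] = 0.01223. Power = Φ[(0.05 − 1.96 × 0.01225) / 0.01223] = Φ(2.13) = 98.3%. The stated 98% is reproduced, so the sample size is not in error.

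**2. The distortion.** Let e1 and e2 be the shares of invitees removed in two arms with equal numbers of participants per 2,500. The observed relative rate, arm 1 over arm 2, is (1 − e2) / (1 − e1). If e1 = e2 it equals 1.

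**3. Removal driven by response.** Assume 15% ineligible in both arms, of whom 40% versus 30% are found, and uptake of 25% of all invited.
- Removed: 0.15 × 0.40 = 6.0% versus 0.15 × 0.30 = 4.5%.
- Rates: 0.25 / 0.940 = 26.6% versus 0.25 / 0.955 = 26.2%, a gap of 0.42 points.
- Relative rate: 0.955 / 0.940 = 1.016.
- SE = √[0.2638 × 0.7362 × (1/2,350 + 1/2,387.5)] = 0.0128. The shift is 0.33 SE and the rejection rate about 6.2%.

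**4. Larger removal gaps, same uptake.**

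| Removed | Rates | Relative rate | Rejection rate |
|---|---|---|---|
| 10% vs 8% | 625/2,250 = 27.8% vs 625/2,300 = 27.2% | 0.92/0.90 = 1.022 | about 7.4% |
| 12% vs 8% | 625/2,200 = 28.4% vs 625/2,300 = 27.2% | 0.92/0.88 = 1.045 | about 15% |

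For the last row the gap is 1.24 points and the SE 0.0134, a shift of about 0.93 SE. A contact gap of 40% versus 30% would produce this 4-point removal gap only if 0.04 / 0.10 = 40% of invitees were ineligible.

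**5. Criteria for CT colonography only.** Suppose 1% of that arm is removed under them and uptake would otherwise be 25%.
- If none of them would have attended: 0.25 / 0.99 = 25.3%, so the rate rises.
- If all would have attended: (0.25 − 0.01) / 0.99 = 24.2%, so the rate falls.

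**6. Against the planned effects.** The planned ratios are 27.5 / 22.5 = 1.22 and 35 / 22.5 = 1.56. The distortion in step 3 would move 1.222 to 1.222 × 1.016 = 1.24. Set against the planned 5-point consultation-mode difference, the gaps of 0.42 and 1.24 points are about 8% and 25% of it.

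**7. Power with everyone invited in the denominator.** If a share q is ineligible in each arm and counted as not participating, the anticipated rates scale by (1 − q). For q = 10%, 20.25% versus 24.75% gives Φ[(0.045 − 1.96 × 0.01181) / 0.01179] = Φ(1.85) = 96.8%. The same formula gives 97.7% at q = 5% and 95.7% at q = 15%. CT colonography versus telephone colonoscopy stays at or above 99.9%, and the overall test above 99%.

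**The case against.** The best defence is that much of the process is shared. The reply routes are the same in all arms and precede the consultation. The checking questionnaire is standardised, general practitioners or specialists can be contacted for any invitee, and most criteria are common. If removal is equal, the ratio is unbiased. Uptake among people for whom screening is intended is also a legitimate quantity: the leaflet tells some ineligible people to stay away, and an all-invited rate counts their compliance as non-participation. Finally, a condensed article may leave the rule for settling eligibility to the full protocol. All of this stands. It supports keeping the eligible-invitee rate, but nothing in the article secures equal ascertainment across arms.

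Three stronger readings are tempting and are not supported:

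- **That eligibility is learned only from people who respond.** The Questionnaires section also describes contact with non-respondents and non-participants, with telephone calls to 10% of non-respondents if response is low. The article does not say that these contacts settle eligibility, but it does not rule it out.
- **That the bias favours telephone over clinic and CT colonography over colonoscopy.** This would follow if the better-responding arm lost more people from its denominator, which is not established. Step 5 shows that the CT-only criteria can act either way.
- **That the type I error is about 15%.** That needs a 4-point removal gap, whereas the response mechanism with 15% ineligible gives about 6%. Both figures also assume that arms differ in removal while having exactly equal uptake. If the invitation affected neither response nor the finding of exclusions, the common criteria would add no bias.

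**Conclusion.** The concern holds, at moderate severity. The denominator stated for participation and yield is settled after allocation, through a process that can differ by arm, so the comparison is not protected by randomisation. Its validity rests on equal removal, which the article does not secure.

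Size and direction cannot be determined from the document. Under the assumed values the spurious relative rate runs from about 1.016 (type I error about 6%) to about 1.045 (about 15%), the upper figure requiring a removal gap of 12% versus 8%. Distortions of this order are unlikely to overturn ratios of 1.22 and 1.56. They matter if the true consultation-mode effect is clearly smaller than the 5 points planned.

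**What to change.** - Compare participation, and yield per 100 invitees, over all persons randomised and invited, counting ineligible persons as non-participants. This also suits the article's aim of predicting what a programme would achieve and cost. People whom CT colonography cannot serve then lower its rate as a real limit on reach.
- Report the eligible-invitee rate beside it, without removing anyone from its denominator for criteria that apply to CT colonography alone.
- Report, by arm, how many were found ineligible and on which criterion, so that readers can judge whether removal was equal.

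This is a change of analysis wording and needs no new data. The cost is slightly lower rates and a small loss of power for the consultation-mode comparison: 97.7%, 96.8% or 95.7% if 5%, 10% or 15% are ineligible, against the stated 98%.

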### Sample size

We anticipate a participation rate of 22.5% in colonoscopy screening with a prior consultation at the screening centre, a participation rate of 27.5% with prior consultation by telephone, and a participation rate of 35% in the CT colonography group (based on the participation rate of FS screening in the Netherlands)[17]. Including 7,500 participants in the trial will then achieve a power exceeding 99% to reject the null hypothesis of no difference, using a 2 degrees of freedom Chi-Square test with a significance level set at 0.05.

These numbers will lead to a 98% power to reject subsequently the hypothesis of no difference in participation for the two consultation modes with direct colonoscopy, and a power exceeding 99% for the two other pair wise comparisons between screening programmes.

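### The deciding chi-square test and the intervals for relative participation do not reflect randomisation by household within age, sex and SES strata

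*Protocol article*

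**What the plan says.** Study design describes the allocation in one sentence: "Randomization will be performed per household, stratified for age, sex and socio-economic status (SES". The same section begins "This study will be a two-centre randomized controlled trial" and draws invitees from the Amsterdam and Rijnmond region, but does not list region among the stratification factors.

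Data analysis names the deciding test: "We will test the null hypothesis of no difference in participation rate using chi-square test statistics". Relative participation rates with 95% intervals are reported against the outpatient-consultation arm, with no adjustment mentioned. The follow-up comparisons are conditional on rejecting the overall hypothesis. A model is added: "We will also calculate a conditional relative participation rate using logistic regression modelling, accounting for baseline variables". Its covariates are not named.

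Sample size powers the unadjusted test, "using a 2 degrees of freedom Chi-Square test with a significance level set at 0.05", with 2,500 invitees per arm. Neither section mentions the household.

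**The concern.** An analysis should follow the way the units were allocated, and here it departs from the allocation in two ways.

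- **Strata.** Stratified allocation balances the arms on age, sex and SES. A plain chi-square still counts variation between strata as random error, so on this ground alone it is slightly conservative.
- **Households.** Housemates who are both invited share an arm. If they tend to decide alike, they carry less information than two independent invitees, and a plain chi-square is anti-conservative.

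At stake are the stated 5% error rate and the stated 95% coverage for the primary outcome. The document names this test and powers it, so the choice is fixed in the text and is not a detail left open. The logistic model does not repair it. It sits beside the test, it does not control the testing sequence, and nothing says that it contains the stratification factors or allows for households.

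**Working it through.** **1. The plan's own figure.** Inputs from Sample size are the expected uptake in each arm: 22.5% (colonoscopy, clinic visit first), 27.5% (colonoscopy, telephone call first) and 35% (CT colonography). With n = 2,500 per arm and two-sided alpha 0.05, for 22.5% against 27.5%:

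- SE under the null = sqrt(2 × 0.25 × 0.75 / 2500) = 0.01225.
- SE under the alternative = sqrt((0.225 × 0.775 + 0.275 × 0.725) / 2500) = 0.01223.
- z = (0.05 − 1.96 × 0.01225) / 0.01223 = 2.13, so power = 98.3%. The stated 98% reproduces.
- The overall 2-df test has noncentrality 97.5 and power above 99.99%. The other two pairwise powers are 99.99% or more, consistent with the text.

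**2. Strata alone.** Let f = (between-stratum SD)² / (p(1 − p)) with p = 0.25, so p(1 − p) = 0.1875. The correct variance is (1 − f) times the unadjusted one. The true error of a nominal 5% pairwise test is 2P(Z > 1.96/√(1 − f)). The SDs are assumptions; the document gives none.

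| SD (points) | f | SE too large by | Type I error | Power if adjusted |
|---|---|---|---|---|
| 3 | 0.0048 | 0.2% | 0.0495 | 98.4% |
| 5 | 0.0133 | 0.7% | 0.0485 | 98.4% |
| 8 | 0.0341 | 1.8% | 0.046 | 98.6% |
| 10 | 0.0533 | 2.8% | 0.044 | 98.7% |

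**3. Strata and households together.** Assume two-person households. Let s be the share of invitees whose housemate is also invited and ICC the correlation of housemates' decisions. The variance factor is V = (1 − f) + s(ICC − f), and the type I error is 2P(Z > 1.96/√V). The grid takes SD 5, 8 and 10 points, s = 10%, 20%, 30% and 50%, and ICC = 0.1, 0.3 and 0.5, all assumed.

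- Lowest: SD 10, s = 10%, ICC 0.1 gives V = 0.951 and type I error 0.044.
- Middle: SD 5, s = 30%, ICC 0.3 gives V = 0.9867 + 0.3 × 0.2867 = 1.073 and type I error 0.058.
- Highest: SD 5, s = 50%, ICC 0.5 gives V = 1.23 and type I error 0.077. Power with a valid test is then 95.7%, the lowest in the grid.
- V exceeds 1 in 23 of the 36 combinations. That count reflects the values chosen and is not a probability.

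**4. Where the two effects cancel.** V = 1 when s = f/(ICC − f). Suppose uptake varies by ±10 points over five SES classes, ±5 by age and ±1.5 by sex. Then f = (0.0050 + 0.0025 + 0.000225)/0.1875 = 4.1%. With ICC = 0.3, s = 0.041/0.259 = 16%. Above that share the plain test is anti-conservative.

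**5. Simulation of the 2-df chi-square under the null** (30 strata, 4,000 runs per scenario, ICC applied within strata). Type I error was 0.051 with no structure, and 0.051 and 0.039 with strata only (SD 5 and 10). With households it was 0.058, 0.071, 0.064 and 0.086 for SD/s/ICC of 5/20%/0.3, 5/30%/0.5, 8/30%/0.3 and 8/50%/0.5. The pattern agrees with the formula.

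**6. Effect on an interval.** At the planned rates the relative rate is 27.5/22.5 = 1.222, with unadjusted 95% interval 1.110 to 1.346. Removing the strata variance at SD 5 gives 1.110 to 1.345. A net variance factor of 1.10 gives 1.104 to 1.353, and 1.25 gives 1.097 to 1.362.

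**The case against.** The strongest reply is that an unadjusted chi-square with a supportive adjusted model is a common pre-specified analysis, that it matches the powered test, and that the choice of covariates is something a full protocol or analysis plan settles. On the strata alone most of this stands: the gain is under half a point on 98% power, every gradient is assumed, and no conclusion at the planned differences would change. It does not answer the household part. Allocating by household has consequences only if members of one household can both be invited, and the stated test treats all invitees as independent.

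A reader might infer a stronger claim: that ignoring the strata makes the intervals too wide and holds the type I error below 5%. The document does not support that net direction, because the sentence that sets the strata also sets the household as the unit. A Cochran-Mantel-Haenszel test on individuals would then be an incomplete remedy: it removes the conservative offset and leaves the clustering. With SD 5 points, s = 30% and ICC 0.3, its type I error is 2P(Z > 1.96 × √(0.9867/1.073)) = 6.0%, against 5.8% for the plain test.

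Two further inferences also lack support. The protocol gives no reasoning about region, so it cannot be said to have considered and rejected it. Nor does it say that all adjustment variables come complete from the municipal register: Study population bases the SES categories on Statistics Netherlands data.

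**Conclusion.** The point holds as a mismatch between the deciding analysis and the randomisation. Its net direction cannot be determined from the document. Strata alone make the standard error about 0.2% to 2.8% too large; households push the other way. Over the assumed grid the type I error lies between about 0.044 and 0.077. These figures rest on assumed stratum spread, share of invited housemates and ICC. If almost no invitee has an invited housemate, only the small conservative effect remains. Sample size is not in question, since power stays above 95% throughout the grid. The consequence is limited to the accuracy of the primary p-values and intervals, and it would matter most if the observed differences were smaller than planned.

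**What to change.** In Data analysis, make the deciding analysis a three-arm comparison adjusted for, or stratified by, age, sex and SES, with standard errors robust to household clustering. A GEE or a modified Poisson or log-binomial model clustered on household would serve. It yields relative participation rates with 95% intervals, a 2-df overall test and the planned pairwise contrasts. Region may be added as a covariate for precision. Name the covariates and keep the unadjusted chi-square as supportive.

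The cost is slightly more analysis work, a household identifier carried into the analysis file, possible merging of sparse strata, and intervals that may be slightly wider once clustering is counted. Design and sample size do not change.
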